# Early-start antiplatelet therapy after operation in patients with spontaneous intracerebral hemorrhage and high risk of ischemic events (E-start): Protocol for a multi-centered, prospective, open-label, blinded endpoint randomized controlled trial

**DOI:** 10.3389/fnagi.2022.1020224

**Published:** 2022-11-23

**Keywords:** severe spontaneous intracerebral hemorrhage, antiplatelet therapy, postoperative management, major cardiovascular/cerebrovascular and peripheral vascular events, randomized controlled trial

## Abstract

**Background:**

For severe spontaneous intracerebral hemorrhage (sSICH) patients with high risk of ischemic events, the incidence of postoperative major cardiovascular/cerebrovascular and peripheral vascular events (MACCPE) is notable. Although antiplatelet therapy is a potential way to benefit these patients, the severe hemorrhagic complications, e.g., intracranial re-hemorrhage, is a barrier for early starting antiplatelet therapy.

**Objectives:**

This randomized controlled trial aims to identify the benefit and safety of early starting antiplatelet therapy after operation for sSICH patients with high risk of ischemic events.

**Methods:**

This study is a multicenter, prospective, randomized, open-label, blinded-endpoint trial. We will enroll 250 sSICH patients with a high risk of ischemic events (including cerebral infarcts, transient ischemic attack, myocardial infarction, pulmonary embolism, and deep venous thrombosis). The participants will be randomized in a 1:1 manner to early-start group (start antiplatelet therapy at 3 days after operation) and normal-start group (start antiplatelet therapy at 30 days after operation). The early-start group will receive aspirin 100 mg daily. The control group will not receive antithrombotic therapy until 30 days after operation. The efficacy endpoint is the incidence of MACCPE, and the safety endpoint is the incidence of intracranial re-hemorrhage.

**Discussion:**

The Early-Start antiplatelet therapy after operation in patients with spontaneous intracerebral hemorrhage trial (E-start) is the first randomized trial about early start antiplatelet therapy for operated sSICH patients with a high risk of ischemic events. This study will provide a new strategy and evidence for postoperative management in the future.

**Clinical trial registration:**

ClinicalTrials.gov, identifier NCT04820972; Available at: https://clinicaltrials.gov/ct2/show/NCT04820972?term=NCT04820972&draw=2&rank=1.

Chinese Clinical Trial Registry, identifier ChiCTR2100044560; Available at: http://www.chictr.org.cn/showproj.aspx?proj=123277.

## Introduction

Severe spontaneous intracerebral hemorrhage (sSICH), characterized by a massive intracerebral hemorrhage and coma, is the most acute subtype of hemorrhagic stroke, with considerable disability and mortality (Cordonnier et al., 2018; Gross et al., 2019). Notably, sSICH patients are characterized by old age and usually have ischemic-arterial-related comorbidities (Wu et al., 2021). Although surgical treatment can improve the outcome and reduce the mortality of sSICH patients (Luzzi et al., 2019; Wu et al., 2021), they are still threatened by the risk of ischemic artery events postoperatively, e.g., major cardiovascular/cerebrovascular/peripheral vascular events (MACCPE; Kumar et al., 2010; Devereaux and Sessler, 2015; Smilowitz and Berger, 2016; Goshgarian and Gorelick, 2017; Smilowitz et al., 2017; Smilowitz and Berger, 2020).

In high-and middle-income countries, about a quarter of spontaneous intracerebral hemorrhage patients received antiplatelet therapy before hemorrhage (Lovelock et al., 2007). Moreover, for patients suffering from spontaneous intracerebral hemorrhage, ischemic artery events are the important factor related to the long-term poor outcome (Flynn et al., 2010; Pennlert et al., 2014; Poon et al., 2014; Casolla et al., 2019; Parasram et al., 2022). However, after hemorrhage, discontinuation of antiplatelet therapy, abnormal cardia-cerebrovascular hemodynamics and bedridden condition will certainly increase the risk of MACCPE (Devereaux and Sessler, 2015; Smilowitz and Berger, 2016; Goshgarian and Gorelick, 2017; Smilowitz et al., 2017; Ding et al., 2019; Smilowitz and Berger, 2020). Our previous study showed that approximately 20% sSICH patients had a history of antiplatelet therapy and ischemic artery events occurred in more 10% patients (Wu et al., 2021). The incident rate of MACCPE may be higher in the sSICH patients with high risk of ischemic artery events. Thus, timely and appropriate antiplatelet therapy may helpful to prevent the ischemic events and improve the outcome of sSICH patients.

Some studies reported that antiplatelet therapy might be an effective way to prevent MACCPE (Tran and Anand, 2004; Ding et al., 2018). However, the status quo is that there were just a few studies and clinical trials for perioperative management of antiplatelet therapy. Thus, no reliable protocol has been promoted to indicate when and how a sSICH patient could receive the antiplatelet therapy after appropriate surgical treatment. Considering the ischemic artery events usually occurred within 1 month after hemorrhage (Murthy et al., 2020), we assume that early antiplatelet therapy can prevent sSICH patients from MACCPE.

Here, we prepare to conduct a randomized controlled trial, aiming to investigate the efficacy and safety of early starting antiplatelet therapy in sSICH patients with high risk of ischemic artery events, postoperatively. This study will provide an evidence-based medical basis for postoperative management of antiplatelet therapy.

## Materials and methods

### Study design

This study is a multicenter, prospective, randomized, open-label, blinded-endpoint trial, which begins in May 2021, and is scheduled to be completed by May 2023. After operation, sSICH patients with high risk of ischemic events will be randomized in a 1:1 manner to early start group (start antiplatelet therapy at postoperative 3 days) and normal start group (start antiplatelet therapy at postoperative 30 days). The primary efficacy endpoint is the incident of MACCPE, and safety endpoint is the incident of re-hemorrhage. This randomized controlled trial (RCT) will follow the Consolidated Standards of Reporting Trials (CONSORT) guidelines.

### Patient selection

The inclusive/exclusive criteria are shown in Table 1. Patients suffering from sSICH, aged 18~70 years, will be screened after operation. Firstly, we will exclude patients (1) with brain tumors and cerebrovascular diseases (e.g., arteriovenous malformation and intracranial aneurysm); (2) with a history of salicylic acid allergy; (3) with hemorrhagic transformation subtype of stroke; (4) with secondary hemorrhage of venous embolism; (5) with malignant tumors; (6) receiving antithrombic therapy regardless of antiplatelet therapy; (7) with thrombocytopenia or coagulopathy disorders, and (8) with a history of atrial fibrillation. The reminded patients will receive an evaluation to identify the serum total cholesterol level, HDL cholesterol before randomization. The sSICH patients with the high postoperative risk of ischemic artery events will be enrolled into a according to follow criteria: (1) patients have a history of cerebral infarction or transient ischemic attack (TIA); (2) patients have a history of coronary heart disease or myocardial infarction; (3) ASCVD Risk Estimator Plus (Muntner et al., 2014; Cook and Ridker, 2016; Lloyd-Jones et al., 2019; mainly consider age, sex, race, systolic blood pressure, diastolic blood pressure, total cholesterol, HDL cholesterol, history of diabetes, smoker, on hypertension treatment): 10-year risk > 10% (Society CS, 2016); (4) The Caprini Risk Scale > 2 (Caprini et al., 1991; Obi et al., 2015). Patients should meet any one of the first three criteria and meet the fourth criteria simultaneously. If a sSICH patient have a new occurrence of cerebral infarction or intracerebral hemorrhage, venous thrombus embolism or acute coronary syndrome within 3 days after operation, they will be not considered in subsequent randomization.

**Table 1 tab1:** The inclusive/exclusive criteria.

**Inclusion criteria** Aged 18–70 years^*^ Nontraumatic spontaneous intracerebral hemorrhage^*^ Patients with postoperative high risk of MACCPE^*^ Previous history of cerebral infarction or TIA. Previous history of coronary heart disease or myocardial infarction. ASCVD Risk Estimator Plus: 10 years risk > 10%. The Caprini Risk Scale: Score > 2. Received neurosurgical procedures Signed informed consent. No history of allergy to salicylic acid preparation.^*^ Complete the preintervention assessment and meet the fellow criteria: Postoperative head CT showed no new infarction or hemorrhage Postoperative venous ultrasound of the lower extremity did not reveal deep vein thrombosis Postoperative electrocardiogram and myocardial enzyme examination did not show acute myocardial ischemia or myocardial infarction.
**Exclusion criteria** Structural cerebrovascular lesions (such as intracranial aneurysms, cerebrovascular malformations, etc.) or tumors in the area of bleeding or the bleeding is suspected to be related to these lesions Ischemic stroke with hemorrhagic conversion Secondary bleeding due to venous embolism The malignant tumor is expected to have a survival of no more than 3 months. Take antithrombotic agents, such as Vitamin K antagonists (warfarin) or new anticoagulants (Dabigatun Rivaroxaban) in addition to antiplatelet agents. Previous history of thrombocytopenia or coagulation disorders. Previous history of atrial fibrillation. Antiplatelet-related intracerebral hemorrhage Cerebral amyloid angiopathy-related intracerebral hemorrhage

* The inclusion criteria of primary screening.

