### Endpoints and relative definitions

The primary efficacy endpoint is the incidence of MACCPE after operation. The MACCPE event is identified when patients suffer from a new cerebral infarct outside the surgical area, enlarging cerebral infarction area, new-onset TIA, more frequent TIA, new-onset myocardial infarction, reperfusion therapy for original myocardial infarction, pulmonary embolism, or deep venous thrombosis.

The other outcomes included: (1) the 3-month mortality after surgery; (2) in-hospital mortality; (3) 30- and 90-day neurological function after operation, which is assessed using the modified Rankin scale (van Swieten et al., 1988) (mRS) or Glasgow outcome scale (Jennett and Bond, 1975; GOS).

The safety endpoint is the incidence of hemorrhagic complications during antiplatelet therapy, i.e., the radiological re-hemorrhage of the operative region (comparing with the preoperative or postoperative first images) or new occurrence of intracerebral hemorrhage, subdural hemorrhage, subarachnoid hemorrhage or intraventricular hemorrhage.

For the cerebral infarcts, immediate CT (due to sudden or continuously deteriorating neurological state) and regular follow-up CT (postoperative 7 ± 5 days, postoperative 90 ± 10 days) will screen new hypodense lesions. If new hypodense lesions are found, an MRI will be used to determine the lesions. New cerebral infarcts outside the surgical area were defined as new hypodense lesions on T2-weighted MRI, which are visible in at least two continuous views. Enlarging infarctions were defined as an increase in a previously existing area of T2-weighted signal hyperintensity of at least 3 mm in one dimension (Vendt et al., 2009).

Transient ischemic attack (TIA) was defined as a transient episode (duration of symptoms < 24 h) of neurological dysfunction caused by focal brain, spinal cord, or retinal ischemia without showing acute infarction on CT images. The primary endpoint was met if patients presented with new-onset TIA or more frequent TIA.

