#### Step 1: Screening and enrollment

As shown in Figure, patients will receive a primary screening before operation. The evaluation includes head computational tomography (CT), deep venous ultrasound, coagulation and myocardial enzyme examination. The patients with (1) re-hemorrhage or residual hematoma expansion, (2) deep vein thrombosis, and (3) abnormality in myocardial enzymes examination.

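### The primary endpoint is counted from the operation although randomisation is on day 3, and no screen removes an early TIA, so a patient can be randomised with the endpoint already met

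*Protocol article*

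**What the plan says.** **Endpoint clock.** Endpoints and relative definitions states: "The primary efficacy endpoint is the incidence of MACCPE after operation". The same section adds TIA as a sufficient event: "The primary endpoint was met if patients presented with new-onset TIA or more frequent TIA". The blinded assessment of MACCPE and re-hemorrhage is also timed from surgery (10 ± 4 and 90 ± 14 days). The routine CT for infarcts is set at postoperative 7 ± 5 days.

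**Allocation.** Study design describes the "early start group (start antiplatelet therapy at postoperative 3 days"). Table 3 marks both randomisation and the start of antiplatelet therapy in the day-3 column.

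**Screens before randomisation.** These appear in three places:
- The text of Patient selection excludes patients with a "new occurrence of cerebral infarction or intracerebral hemorrhage, venous thrombus embolism or acute coronary syndrome within 3 days after operation".
- Table 1 requires, among other things, "Postoperative head CT showed no new infarction or hemorrhage" and "Postoperative venous ultrasound of the lower extremity did not reveal deep vein thrombosis", plus an ECG and enzymes without acute ischemia or infarction.
- Step 1 lists "The patients with (1) re-hemorrhage or residual hematoma expansion, (2) deep vein thrombosis, and (3) abnormality in myocardial enzymes examination". That sentence has no verb, so its force is unclear.

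**The concern.** In a randomised comparison, outcome counting should start at allocation. Here it starts at the operation, three days earlier. This would be harmless if the pre-randomisation screens removed every event that counts as an endpoint, because nobody could then enter with an event behind them. They remove most such events but not all.

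An event that precedes allocation can be neither caused nor prevented by the choice of aspirin start. If it is counted, it adds the same expected number of events to both arms, shrinks the relative effect and costs power.

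**Working it through.** **1. Does the endpoint window open before randomisation?**
- Primary endpoint: from the operation, day 0.
- Blinded assessment: timed from surgery.
- Routine infarct CT: 7 − 5 = day 2 at the earliest.
- Randomisation and first aspirin: day 3.

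The window opens before randomisation on each of these clocks. Step 3 times the MACCPE examinations from the first aspirin dose instead. Under Step 2, however, the normal-start arm receives no antithrombotic therapy before day 30, so that clock has no corresponding start in controls.

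**2. Which MACCPE components do the screens cover?**

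| Component | Covered before randomisation? |
|---|---|
| New cerebral infarct | Yes (Patient selection text; Table 1 CT) |
| New myocardial infarction | Yes (acute coronary syndrome in the text; Table 1 ECG and enzymes) |
| Deep venous thrombosis | Yes (text; Table 1 ultrasound; Step 1) |
| Pulmonary embolism | Only through venous thromboembolism in the text |
| New-onset or more frequent TIA | No |
| Enlarging infarct | Not named |
| Reperfusion for an original myocardial infarction | Not named |

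The CT criterion cannot catch a TIA, because the article defines TIA by the absence of acute infarction on CT. A history of infarction, TIA or coronary disease is among the qualifying criteria, so the worsening-type components apply to part of the enrolled population.

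**3. How large could the effect be?**

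Inputs from Sample size: control incidence 10.8%; a reduction of 5%, read as absolute, so 10.8% to 5.8%; 125 per arm. The two-sided 5% level is from the statistical analysis section. The planning risk ratio is 5.8/10.8 = 0.537.

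The article's own total of 244 is not reproduced from these inputs. The pooled two-proportion formula gives 954 in total for 80% power, and 125 per arm gives 29.8%. That is a separate matter and only sets the starting point here.

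The documents give no event rate for days 0–3. Let q be an assumed share of patients with a counted pre-randomisation event, equal in both arms. The 10.8% is already an incidence after operation, so the control total is held there. Then:

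- early-start rate = q + (0.108 − q) × 0.537
- example, q = 1%: 0.010 + 0.098 × 0.537 = 0.0626; risk ratio 0.0626/0.108 = 0.580
- power = Φ{[Δ√n − 1.96√(2p̄(1 − p̄))] / √(p₁(1 − p₁) + p₂(1 − p₂))}, with n = 125, Δ = p₁ − p₂ and p̄ the mean of the two rates

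| q (assumed) | Early-start rate | Difference | Risk ratio | Power, 125 per arm | Total N for 80% |
|---|---|---|---|---|---|
| 0 | 5.80% | 5.00 points | 0.537 | 29.8% | 954 |
| 0.5% | 6.03% | 4.77 points | 0.558 | 27.3% | 1062 |
| 1% | 6.26% | 4.54 points | 0.580 | 24.9% | 1188 |
| 2% | 6.73% | 4.07 points | 0.623 | 20.5% | 1510 |

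In patients, q of 0.5% to 2% is 250 × 0.005 = 1.25 to 250 × 0.02 = 5 across the trial. As a share of control events it is 0.5/10.8 = 5% to 2/10.8 = 19%.

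If the early events instead came on top of 10.8%, q = 2% would give 0.02 + 0.98 × 0.108 = 12.6% against 0.02 + 0.98 × 0.058 = 7.7%. The risk ratio would be 0.61 and the power 24.9%: the same direction, with a smaller loss.

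**The case against.** **The number of such events is probably small.** The Discussion reports that MACCPE in the sponsor's cohort begins around postoperative day 4 and peaks on day 7. The Introduction describes these patients as comatose, and a transient focal deficit is hard to recognise in coma. This stands. It makes the upper end of the table unlikely, and every q in it is an assumption.

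**The procedure already evaluates outcomes after randomisation.** The steps run screening, randomisation, outcome evaluation, and Step 3 times the examinations from aspirin. Counting from the operation could therefore be article shorthand. This stands only in part. The aspirin clock does not exist for controls before day 30, and the blinded assessment is stated from surgery.

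**Pre-allocation events are balanced in expectation.** This stands. The expected harm is dilution, not bias. A reader might infer uneven counting between arms because the trial is open-label, or because sites apply different rules. The documents do not support that: they describe no site-specific rules, and two investigators blinded to patient information assess the events.

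**A stronger reading concerns bleeding.** Patient selection names only intracerebral hemorrhage, while the safety endpoint also covers "new occurrence of intracerebral hemorrhage, subdural hemorrhage, subarachnoid hemorrhage or intraventricular hemorrhage". A reader might infer that a patient with an early subdural, subarachnoid or intraventricular bleed can enter with the safety endpoint already met. The documents do not support this. Table 1 requires a CT without any new hemorrhage, so such a patient is not eligible. The safety endpoint is also limited to the period of antiplatelet therapy, which a day-2 bleed precedes. These bleeds are not part of MACCPE either. What remains is a difference in wording between the screens.

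**Conclusion.** The point holds for the primary efficacy endpoint. As worded, MACCPE counts from the operation, randomisation is on day 3, and TIA appears in no pre-randomisation screen. Infarct enlargement and reperfusion for an original infarction are not named in the screens either. A randomised patient can therefore already have met the primary endpoint.

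The consequence is modest dilution. For an assumed share of 0.5% to 2%, the risk ratio moves from 0.54 to 0.56–0.62 and power with 125 per arm from about 30% to 27–21%. This rests on the absolute reading of the 5% reduction, a control total fixed at 10.8%, equal shares in both arms and an assumed q. The article's own timing data favour the low end. It is a defect in how the primary endpoint is fixed, worth correcting because the correction is nearly free.

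**What to change.** In Endpoints and relative definitions, define MACCPE as events with onset after randomisation in both arms, in the endpoint definition and in the sentence on blinded assessment. Record a TIA on days 0–3 as baseline status, so that a later new-onset or more frequent TIA is judged against the patient's state at randomisation. Apply the same rule to infarct enlargement and to reperfusion for an original myocardial infarction.

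The text of Patient selection, Table 1 and Step 1 word the pre-randomisation screen differently, for example intracerebral hemorrhage in one place and any new hemorrhage on CT in another. The sponsor must reconcile them. Once the clock is changed, a new TIA exclusion is not needed for the analysis. Whether such patients should be eligible is for the sponsor to decide.

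Cost: a few words. The article already has investigators record the time of each MACCPE, so no new data are needed. The downside is a slightly lower observed event rate.

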### Endpoints and relative definitions

The primary efficacy endpoint is the incidence of MACCPE after operation. The MACCPE event is identified when patients suffer from a new cerebral infarct outside the surgical area, enlarging cerebral infarction area, new-onset TIA, more frequent TIA, new-onset myocardial infarction, reperfusion therapy for original myocardial infarction, pulmonary embolism, or deep venous thrombosis.

The other outcomes included: (1) the 3-month mortality after surgery; (2) in-hospital mortality; (3) 30- and 90-day neurological function after operation, which is assessed using the modified Rankin scale (van Swieten et al., 1988) (mRS) or Glasgow outcome scale (Jennett and Bond, 1975; GOS).

The safety endpoint is the incidence of hemorrhagic complications during antiplatelet therapy, i.e., the radiological re-hemorrhage of the operative region (comparing with the preoperative or postoperative first images) or new occurrence of intracerebral hemorrhage, subdural hemorrhage, subarachnoid hemorrhage or intraventricular hemorrhage.

For the cerebral infarcts, immediate CT (due to sudden or continuously deteriorating neurological state) and regular follow-up CT (postoperative 7 ± 5 days, postoperative 90 ± 10 days) will screen new hypodense lesions. If new hypodense lesions are found, an MRI will be used to determine the lesions. New cerebral infarcts outside the surgical area were defined as new hypodense lesions on T2-weighted MRI, which are visible in at least two continuous views. Enlarging infarctions were defined as an increase in a previously existing area of T2-weighted signal hyperintensity of at least 3 mm in one dimension (Vendt et al., 2009).

Transient ischemic attack (TIA) was defined as a transient episode (duration of symptoms < 24 h) of neurological dysfunction caused by focal brain, spinal cord, or retinal ischemia without showing acute infarction on CT images. The primary endpoint was met if patients presented with new-onset TIA or more frequent TIA.

Myocardial infarction is defined as myocardial necrosis in a clinical setting consistent with myocardial ischemia. These conditions can be satisfied by a rise of cardiac biomarkers (preferably cardiac troponin [cTn]) plus at least one of the following: (1) symptoms of cardiovascular ischemia; (2) ECG changes indicative of new ischemia (significant ST/T changes or left bundle branch block); (3) development of pathologic Q waves; (4) imaging evidence of new loss of myocardium or new regional wall motion abnormality; (5) angiography or autopsy evidence of intracoronary thrombus.

The patients who had CT pulmonary angiography or autopsy evidence of pulmonary embolism were defined as pulmonary embolism. For the patients who had no evidence, if they fulfilled the criteria described below, they were also defined as pulmonary embolism. The criteria include (1) clinical manifestations of pulmonary embolism: cough, chest pain, hemoptysis, dyspnea, etc.; (2) Wells score > 4; (3) blood tests showed high D-dimer levels, high Troponin levels, low blood oxygen saturation, high alveolar-arterial (A-a) oxygen partial pressure; (4) venous ultrasound of lower extremities showed deep vein thrombosis.

Deep venous thrombosis was defined as the follow-up venous ultrasound of lower extremities that showed hyperechoic or mixed echogenicity in deep venous. Deep veins mainly include femoral vein, popliteal vein, anterior tibial vein, posterior tibial vein, fibular vein, and iliac vein.

Re-hemorrhage of the operative region was defined as new high-density focal lesions in the surgical area or original hematoma enlargement comparing with the preoperative CT and first postoperative CT. Postoperative subdural hemorrhage, subarachnoid hemorrhage, and intraventricular hemorrhage were also confirmed by postoperative CT.

Two investigators will identify blinded to the patient information assesses the occurrence of MACCPE and rehemorrhage events on 10 ± 4 and 90 ± 14 days post-surgery. mRS scores, GCS, and GOS will be assessed on 30 days/discharge and 90 ± 14 days post-surgery.

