#### Step 3: Outcome evaluation

During hospital stay, patients will receive a series of special examinations of MACCPE at 10 ± 4 days after administration of aspirin, in order to identify whether there is an occurrence of MACCPE. If patients have a sudden unconsciousness, or suddenly or gradually worsening neurological states after administration of aspirin, a head CT examination will be conducted immediately to identify whether there is an occurrence of re-hemorrhage. If the patient occurs ischemic events, the antiplatelet or anticoagulation therapy will be added to the patient based on the specific condition. These patients meet the endpoint when ischemic events occur, so they will not be excluded from this study.

Patients will be regularly followed up at 30 and 90 days. To the patient who did not discharge in 30 days, we would assess the clinic score at the bedside. To the discharged patient, we assess the clinic score *via* outpatient or phone review. At 90 days, if the patient could not complete the follow-up examination in the medical centers involved to the study, they will be required to complete the relative examinations in the local hospitals. Our investigators will ask patients’ family members to upload the follow-up data and assess the quality of these data. If these data are out of required quality and more details could not be got, the patients will be considered as the patients withdrawing from the follow-up (Figure 2).

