### Statistical analysis

#### Sample size

The sample size is estimated using the PASS 15 (PASS corporation, United States). In our preliminary study, we investigated the clinical characteristics and outcome of operated sSICH patients in Beijing Tiantan Hospital. The incidence of main adverse cardiovascular and cerebrovascular events was 10.8% after operation (Wu et al., 2021). The E-start study expects to reduce the incident of MACCE by 5%. Patients were randomized at a ratio of 1:1 to one of two groups. At (1 − β) as 0.8 and α as 0.05, 244 consecutive patients would be enrolled in this study (122 in the early start group and 122 in the normal start group). This study prepares to enroll 250 operated sSICH patients, including 125 subjects in the early start group and 125 subjects the normal start group.

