## Discussion

E-start study is the first clinical trial of postoperative early start antiplatelet therapy in sSICH patients with high risk of ischemic events. In this study, we investigate whether early start antiplatelet therapy after surgery can prevent the incident of MACCPE, with no increasing risk of postoperative intracranial rehemorrahge.

Early start antiplatelet therapy postoperatively may reduce the incidence of MACCPE that seriously affects the clinical outcome of sSICH patients (Ding et al., 2018). However, there is no standardized protocol for postoperative antiplatelet management. Therefore, we analyzed the characteristics of postoperative MACCPE incidence by the SAP-ICH cohort (ChiCTR1900024406). We find that MACCPE occurs four postoperative days later, and the peak is the seventh day after surgery. Remarkably, there were often more than 30 days before starting antiplatelet therapy postoperatively in past research (Flynn et al., 2010; Murthy et al., 2019; RESTART Collaboration, 2019). Therefore, it may be missing the time window of the high incidence of MACCPE, which may mask treatment effects. Summarily, early start antiplatelet therapy (start in postoperative 4 days) is crucial for decease the incidence of MACCPE.

Notably, safety is another consideration in this study. The data of SAP-ICH showed that intracerebral hemorrhage events often occur 3 days following the procedure. In addition, many studies have reported the results that restarting antiplatelet therapy after ICH does not increase the risk of recurrent intracerebral hemorrhage (Flynn et al., 2010; Teo et al., 2017; Chen et al., 2018; Murthy et al., 2019; RESTART Collaboration, 2019; Diep and Garcia, 2020; Al-Shahi Salman et al., 2021). The results of an observational study published in *stroke* showed that the rate of recurrent bleeding after discharge in sSICH patients treated with antiplatelet agents was roughly the same as that in patients not treated with antiplatelet agents (Flynn et al., 2010). The “RESTART” research, a randomized controlled study published in the Lancet, further confirmed that the risk of a recurrent intracerebral hemorrhage after SICH using antiplatelet therapy is small (RESTART Collaboration, 2019). However, this assumption should be verified by the result of this study.

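### The written deep vein thrombosis (DVT) endpoint rests on echo texture alone, so a recent dark thrombus at the first follow-up scan does not meet it, and no comparison with the entry scan is required

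*Protocol article*

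**What the plan says.** In the protocol article, Endpoints and relative definitions, the composite ends with "reperfusion therapy for original myocardial infarction, pulmonary embolism, or deep venous thrombosis". The same section then gives the operational rule: DVT is a follow-up leg ultrasound that "showed hyperechoic or mixed echogenicity in deep venous". A list of the deep veins concerned follows. Nothing elsewhere in the article adds compressibility, a filling defect, absent flow or a dark thrombus to this rule.

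On entry, Table 1 requires: "Postoperative venous ultrasound of the lower extremity did not reveal deep vein thrombosis". The Patient selection text also keeps out patients with new venous thromboembolism in the first 3 days after operation, and Step 1 includes a deep venous ultrasound at primary screening. None of these places states a sonographic criterion.

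On timing, Step 3 says "patients will receive a series of special examinations of MACCPE at 10 ± 4 days after administration of aspirin". Table 2 lists leg venous ultrasound among these examinations. Table 3 schedules them within 72 hours, at 10 ± 4 days and again at 90 days. The Discussion says of the composite: "We find that MACCPE occurs four postoperative days later, and the peak is the seventh day after surgery".

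**The concern.** An endpoint definition decides which findings the blinded assessors may count. This one makes bright or mixed echo texture both necessary and sufficient. Thrombus tends to brighten as it ages. In its first days it is often dark and is recognised because the vein does not compress or carries no flow. The rule therefore fits worst the clots that the trial hopes to prevent, those arising in the days after randomisation.

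The second weakness is the missing link to baseline. Infarction, TIA and myocardial infarction count when they are new, enlarging or more frequent, and re-hemorrhage is judged against earlier CT. DVT has no such condition.

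At stake are true events in a composite with few expected events, and consistent scoring between centres. If assessors call DVT by ordinary practice, they depart from the written endpoint, and centres may depart from it differently.

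**Working it through.** The plan gives no figure on this point to reproduce. The check is mainly a comparison of texts.

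**1. Age of a new clot at the first follow-up scan.** The article anchors the 10 ± 4 days in two ways.
- From surgery (Endpoints and relative definitions): postoperative days 6 to 14.
- From the start of aspirin (Step 3), with the start at day 3: postoperative days 3 + 6 = 9 to 3 + 14 = 17.

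The maximum age of a clot is the latest scan day minus the day it formed.
- Formed just after day 3: 14 − 3 = 11 days, or 17 − 3 = 14 days.
- Formed at day 7, the peak for the composite: 14 − 7 = 7 days, or 17 − 7 = 10 days.

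On either anchor, new DVT at this scan is recent.

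**2. Entry check against endpoint.** The entry criterion is not stated, so there are two cases.
- Entry uses the same texture rule: old bright clots are screened out, but a dark clot passes. It can meet the endpoint once it brightens.
- Entry uses ordinary ultrasound diagnosis: bright and dark clots are both screened out, but entry and endpoint then follow different rules.

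In neither case should an old bright clot reach randomisation. The carry-over of a dark clot arises only in the first case.

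**3. Effect of equal under-detection.** Let a share s of true DVT be detected in both arms. The observed rates are s·p_C and s·p_E. The ratio is s·p_E / (s·p_C) = p_E / p_C, unchanged. The difference is s·(p_C − p_E), smaller. With assumed true DVT rates of 10% and 6% and s = 0.5, the observed rates are 5% and 3%. The ratio stays at 0.60, and the difference falls from 4 points to 2.

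**4. Possible effect on the composite (illustration).** Inputs from Sample size: "The incidence of main adverse cardiovascular and cerebrovascular events was 10.8% after operation", a planned reduction of 5%, read here as 5 percentage points (10.8% against 5.8%), and 125 per arm. Assumed: DVT is a share f of events, a share m of DVT is missed in both arms, the relative effect is the same for all components, and each patient has one event. Both rates are then multiplied by k = 1 − f·m.

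Power = Φ{[Δ − 1.96·√(2·p̄(1 − p̄)/n)] / √[(p_C(1 − p_C) + p_E(1 − p_E))/n]}, where Δ = p_C − p_E and p̄ is the mean of the two rates.

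With no loss, Δ = 0.05, p̄ = 0.083 and n = 125: (0.05 − 1.96 × 0.0349)/0.0348 = −0.53, so power is about 30%. Expected events are 125 × 0.108 = 13.5 against 125 × 0.058 = 7.25.

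| f | m | k | Rates | Expected events | Power |
|---|---|---|---|---|---|
| 0.2 | 0.25 | 0.95 | 10.26% v 5.51% | 12.8 v 6.9 | 28.5% |
| 0.4 | 0.50 | 0.80 | 8.64% v 4.64% | 10.8 v 5.8 | 24.4% |
| 0.6 | 0.75 | 0.55 | 5.94% v 3.19% | 7.4 v 4.0 | 17.9% |

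The starting value of 30% lies well below the planned 80%. That is a separate matter about the sample size and does not come from the DVT definition.

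**The case against.** The strongest objection is that the rule is less harmful in use than on paper. Mixed echo texture already admits partly dark thrombus. A clot missed at the first scan may have brightened by day 90 and be counted then. The day-7 peak refers to the whole composite, not to DVT. Scanning technique is also detail that a journal article may leave to the full protocol. The first three points stand and limit the loss. The last does not answer the concern: the article does not leave DVT open but states a complete rule, down to the veins, and the stated rule is what falls short.

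Three stronger readings are tempting, and the documents do not support them.
- A reader might infer that old thrombus counts freely as an event. The definition applies to follow-up scans, and the entry checks should already have removed most old bright clots.
- A reader might infer that the rule pulls the risk ratio towards 1. Equal misses alone do not do this for DVT. It would need false positives in both arms, and the one route left for those is the conditional carry-over of a dark clot from entry.
- A reader might infer that the pulmonary embolism component is equally affected. Its ultrasound item says only "venous ultrasound of lower extremities showed deep vein thrombosis", without repeating the texture rule. It applies where CT angiography or autopsy evidence is absent, and alongside other criteria.

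**Conclusion.** The point holds in limited form. The written endpoint omits recent anechoic or hypoechoic thrombus and does not require that a DVT be new against the entry scan. The consequences are lost true events, a smaller absolute difference and lower power. There is also a carry-over risk if entry uses the same texture rule.

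The amount cannot be fixed from the article, which gives neither the DVT share of the composite nor a detection rate. The fall in power from about 30% to between 29% and 18% shows scale only and rests on the assumed ranges. It ignores recovery at day 90, and the 10.8% comes from a preliminary study whose composite is named without the peripheral vascular part. The conclusion also rests on the general knowledge that thrombus brightens with age. If the relative effect on DVT differs from that on the other components, losing DVT events would also shift the composite ratio, in a direction that the article does not allow one to predict.

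**What to change.** Replace the DVT sentence in Endpoints and relative definitions along these lines: DVT is non-compressibility of a named deep vein segment on ultrasound or, for iliac veins, an intraluminal filling defect or absent flow on Doppler, in a segment that was patent on the pre-randomisation ultrasound. Apply the same criterion to the entry check in Table 1. Record echogenicity as a descriptor only.

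The scans are already scheduled, so the cost is the rewording, one line on the ultrasound form and a short reading reminder to sites. The reminder should also reach local hospitals that perform the day-90 examination. The change concerns how the endpoint is measured and leaves treatment untouched.
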